## METHODS

### Trial design

This study will be carried out in accordance with International Conference on Harmonisation Good Clinical Practice (ICH GCP) and the United States (US) Code of Federal Regulations (CFR) applicable to clinical studies (45 CFR Part 46, 21 CFR Part 50, 21 CFR Part 56, 21 CFR Part 312, and/or 21 CFR Part 812). This Phase II clinical trial will evaluate the performance, preliminary safety and efficacy, and feasibility of rhPDGF-enhanced collagen on healing complex perianal fistulas that are not eligible for a fistulotomy in patients 21 years of age and older. This prospective, blinded, single-site study is expected to enroll and randomize 12 participants at a 2:1 intervention versus control allocation ratio stratified by fistula etiology, idiopathic versus CD-related. The two arms will compare implantation of the rhPDGF-enhanced collagen to routine care procedures, which include COOK Biotech’s Biodesign^®^ Anal Fistula Plug implant for idiopathic fistulas or draining seton removal and natural healing for CD-related fistulas. Following the baseline procedure, patients will be evaluated at Months 1, 3, and 6 to assess healing of the external fistula opening and change in pain, incontinence, and other perianal fistula-related symptoms. Patients randomized to the control group who fail to heal at Month 3 will have the option to crossover to the intervention group and receive the rhPDGF-enhanced collagen intervention. The Standard Protocol Items: Recommendations for Interventional Trials (SPIRIT) schedule of enrollment, intervention, and assessments is included as Figure 1. A graphic study timeline of events is provided in Figure 2. The SPIRIT checklist is included in S1 Appendix. A full accounting of evaluations and unabridged protocol approved by the IRB is available in S2 Appendix (December 13, 2024; version 6.1) and important protocol modifications will be available from the corresponding author and by viewing the ClinicalTrials.gov (NCT06632418) study entry. A sample consent form is included in S3 Appendix.

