#### Exclusion Criteria

Medical conditions that would, in the opinion of the investigator or treating provider, compromise the safety of the individual with study participation and/or the ability of the individual to follow study protocolGenito-urinary fistulization, including rectovaginal (i.e., fistulas that transverse the vaginal canal)Presence of an ileal anal pouchAny major surgery of the gastrointestinal tract (including one or more segments of the colon or terminal ileum) within 3 months prior to randomization; presence of stoma is not exclusionaryPrior surgical procedure (i.e., Ligation of Intersphincteric Fistula Tract or Endorectal Advancement Flap) for the target fistula or a perianal procedure that resulted in a large soft tissue defect within 6 months prior to screening visitOne or more of the following fistula types or anatomic presentations: horseshoe fistulas, fistulas that do not have an opening inside the anal canal or low rectum, blind ending sinus tracts (no external opening), branching fistulas (a previously performed conversion of a branching fistula tract to a single tract is not exclusionary), >1 internal opening, moderate or severe proctitis, severe rectal mucosal fibrosis surrounding the internal opening preventing the securing of the fistula plug disk, any anatomical limitation to successfully securing the fistula plug disk.Known allergic reactions to porcine collagen or yeast-derived productsCurrently enrolled in a drug or device trial or within 30 days of last investigational drug or device administration at baseline visit where investigational treatment (drug or device) was placed in or near the fistula tract or may potentially interact with study treatmentWomen who are known to be pregnant, breastfeeding, or planning to become pregnant, during the trialActive infection at the application siteThe presence of malignant neoplasms at the application sitePrior radiation therapy at the application site

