#### Screen Failures

Screen failures are defined as participants who consent to participate in the clinical trial but are not subsequently randomized or the device is unable to be implanted. A minimal set of screen failure information is required to ensure transparent reporting of screen failure participants, to meet the Consolidated Standards of Reporting Trials (CONSORT) publishing requirements and to respond to queries from regulatory authorities. Minimal information includes demography, screen failure details, eligibility criteria, and any serious adverse event (SAE).

Individuals who consent and do not meet the criteria for participation in this trial (screen failure) because of the following criteria may be rescreened once the below criteria have been resolved.

No draining seton in placeActive infectionSurgical procedures outlined in the exclusion criteriaParticipation in an investigational study as outlined in exclusion criteriaPregnant or breastfeeding

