### Randomization and Blinding

Randomization will occur at the baseline visit at a ratio of 2:1 intervention versus control. Randomization will be stratified to achieve balance in treatment allocation across idiopathic and CD-related fistula types. Because the total sample size is 12, randomization will be blocked using blocks of size 3 (2:1 intervention to control) within each stratum (idiopathic versus CD-related). Based on historical clinical data we anticipate enrolling 9 Chron’s participants and 3 idiopathic participants. Blinding of the patients, surgeons other than the investigator performing the procedure, and study team members assessing outcomes to study arm allocation will be employed to reduce bias in conducting study activities and evaluations. Given that the control group will be receiving a routine care procedure, the investigator who will be performing all procedures will be unblinded to the treatment assignment for each participant. To maintain blinding while assessing outcomes, clinical exams during follow-up study visits will be performed by another surgeon not involved in the initial screening visit or the procedural encounter. In the case of a serious adverse event or medical emergency in which knowledge of the treatment is necessary for the participant’s well-being or medical care, the unblinded investigator will be alerted to ensure appropriate medical management.

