#### Secondary and Tertiary Outcomes Analysis

The secondary efficacy and safety endpoints will be analyzed for all randomized participants, as appropriate. Analyses will not be dependent on the findings of the primary endpoint. The first secondary endpoint considers all treatment-related adverse events and the proportion of participants with such events by arm will be analyzed/reported in the same way as the primary endpoint. The proportion will then be compared across arms using Fisher’s Exact test. If there are at least two participants with multiple treatment-related adverse events, a Mann-Whitney test will compare the number of adverse events per participant across arms.

The next secondary endpoint is fistula healing at Month 3 measured as a binary variable. The probability of healing in each arm will be calculated as the proportion of randomized participants per arm that are diagnosed as completely healed by a clinical evaluation of no visible drainage from the external opening at the Month 3 follow-up visit. The endpoint will be modeled as the outcome in a logistic regression model, conditioning on the treatment arm and baseline etiology. The effect will be presented as an adjusted odds ratio with a 95% confidence interval, as well as the marginal risk ratio after performing standardization. A p-value less than 0.05 will be considered statistically significant, but interpretation will be primarily focused on the 95% confidence interval. Residuals will be inspected to inspect model fit and validity of the homoscedasticity assumption. If model fit is poor, a Fisher’s Exact test will be used in place of logistic regression. Missing data are expected to be limited but will be handled using multiple imputation. Individuals who are lost to follow-up before Month 3 will also be included via the multiple imputation procedure, considering plausible imputations conditional on their baseline and Month 1 follow-up assessments, as well as weekly symptom data. The primary analysis will be modified intention-to-treat (ITT) based on randomized arm, as the investigational product is not available to patients who are not randomized to treatment before the Month 3 outcome assessment. It will be modified ITT in the sense that only participants who receive the investigational intervention will be analyzed as part of the intervention arm; this is necessary as some exclusion criteria cannot be assessed until the time of surgery.

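### The modified ITT rule drops randomized intervention participants who cannot be implanted, with no matching rule for Crohn's controls and an unblinded operator

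*Protocol article*

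**What the plan says.** All places are in the Protocol article.

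- **Secondary and Tertiary Outcomes Analysis.** The analysis follows the randomized arm, modified so that "only participants who receive the investigational intervention will be analyzed as part of the intervention arm". The reason given is that "this is necessary as some exclusion criteria cannot be assessed until the time of surgery". No equivalent sentence is written for controls.
- **Screen Failures.** The term covers consented participants who "are not subsequently randomized or the device is unable to be implanted". The second alternative can apply to someone already randomized.
- **Trial design; Efficacy Assessments.** Idiopathic controls receive a commercial plug. Crohn's controls have the seton removed and the tract debrided, with no implant.
- **Recruitment and Consent.** Anyone who undergoes the baseline procedure counts as treated, in either arm.
- **Participant Discontinuation/Withdrawal.** The investigator may withdraw a participant in whom an exclusion criterion is newly recognized.
- **Randomization and Blinding.** "Randomization will occur at the baseline visit at a ratio of 2:1 intervention versus control", and "the investigator who will be performing all procedures will be unblinded to the treatment assignment for each participant". Nine Crohn's and three idiopathic participants are expected, in blocks of three.

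**The concern.** Eligibility that is settled only at surgery, after assignment, has to be handled identically in both arms. Otherwise the arms stop being comparable in the way that randomization made them. Here an intervention participant found unsuitable at surgery leaves the analysis, while a Crohn's control with the same anatomy can complete the control procedure and stay. The person who judges suitability knows which arm is at stake.

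The estimates at risk are the between-arm secondary comparisons: Month 3 healing, recurrence at Month 6 and symptom change. If unsuitable tracts heal less often, keeping them only among controls favours the intervention. If they heal more often, it works against it. The Discussion says that this pilot is meant to guide a larger efficacy trial, so a distorted healing difference would carry forward.

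**Working it through.** **1. Expected arm sizes** (Randomization and Blinding). Crohn's: 9 participants in blocks of 3 at 2:1 give 3 x 2 = 6 intervention and 3 x 1 = 3 control. Idiopathic: one block gives 2 and 1. The total is 8 and 4, so Crohn's participants are 3 of the 4 expected controls.

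**2. The same surgical finding (implant not feasible) followed through the rules**

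| Stratum, arm | What happens at the procedure | Status in the analysis |
|---|---|---|
| Crohn's, intervention | Implant not placed | Screen failure; not analysed in the intervention arm |
| Crohn's, control | Seton removal and debridement go ahead | Counts as treated; stays in unless the investigator chooses to withdraw |
| Idiopathic, intervention | Implant not placed | Screen failure; not analysed in the intervention arm |
| Idiopathic, control | Commercial plug not placed | The screen-failure rule can apply |

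The gap lies in the Crohn's stratum.

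**3. Is the stated necessity real?** Late-assessed eligibility is a reason to randomize late. Randomization already belongs to the baseline visit, and so does the procedure ("Following the baseline procedure, patients will be evaluated at Months 1, 3, and 6"). Nothing in the article requires the assignment to be known before the examination under anesthesia.

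**4. Reproducing the plan's figures** (Sample Size). The Carlin-Louis interval is taken as the equal-tailed 95% posterior interval for p1 - p0, with p1 ~ Beta(x1 + 1, n1 - x1 + 1) and p0 ~ Beta(x0 + 1, n0 - x0 + 1). The uniform prior is an assumption, chosen because it matches:

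- 7/8 vs 2/4: difference 0.875 - 0.500 = 0.375, lower bound -0.145 (stated about -0.14).
- 8/8 vs 2/4: difference 0.500, lower bound -0.008 (stated -0.01).

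Beta(0.5, 0.5) priors give -0.13 and +0.04 and do not match.

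**5. What symmetric handling would change.** An unsuitable intervention participant is out under the present rule and also when eligibility is settled before assignment. What differs is the unsuitable Crohn's control, who now stays in. Suppose that one of the four controls in the 7/8 vs 2/4 scenario is such a participant, and that the place is not refilled:

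| Case | Healed | Difference | Lower bound |
|---|---|---|---|
| Control kept (present rule) | 7/8 vs 2/4 | 0.375 | -0.14 |
| Taken out, had not healed | 7/8 vs 2/3 | 0.875 - 0.667 = 0.208 | -0.24 |
| Taken out, had healed | 7/8 vs 1/3 | 0.875 - 0.333 = 0.542 | -0.08 |

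One participant moves the difference by 1/6 = 0.167 in either direction (2/3 - 2/4 = 1/6; 2/4 - 1/3 = 1/6).

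**The case against.** **Other text could restore the balance.** The article says that secondary endpoints use all randomized participants, as appropriate, and that healing is a proportion of those randomized. The baseline-procedure rule covers both arms, a clinical examination during the procedure is required without limit to one arm, and withdrawal for a newly recognized exclusion is open to both. This makes the text less than uniform, but it does not close the gap. The modified ITT sentence overrides the general statement for one arm only. A Crohn's control meets the baseline-procedure rule through seton removal. The procedural examination is described as a visual check at the external opening. Withdrawal is discretionary and does not define the analysis set.

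**The full protocol or the SAP may settle it.** That would answer a complaint about missing detail. Here the article itself fixes a one-sided rule and gives a rationale for it.

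**The outcomes are preliminary and the assessors are blinded.** Both are true. The first limits the weight of the point, and the article already concedes low power and difficult interpretation for efficacy. Blinded assessment protects the outcome reading but not selection into the analysis.

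Three stronger readings are tempting and not supported:

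- A reader might take the exclusions for "severe rectal mucosal fibrosis surrounding the internal opening preventing the securing of the fistula plug disk" and "any anatomical limitation to successfully securing the fistula plug disk" as proof that Crohn's arms are tested differently. Intervention and Administration describe a collagen membrane sutured to the rectal mucosa and mention no disk, so no such contrast between the Crohn's arms is shown.
- A reader might see a stricter proctitis threshold at surgery, because the exclusion names moderate or severe disease and the examination names active disease. Whether a different threshold was meant is not stated.
- A reader might size the problem by dropping a non-healer from the intervention arm (7/8 to 7/7), or by refilling that place with a healer (8/8). That compares removal with full ITT. Settling eligibility before assignment would remove the same participant, so it does not measure the asymmetry.

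**Conclusion.** The point holds as a one-sided exclusion after randomization, in the hands of an unblinded operator, that can bias the secondary between-arm comparisons, mainly in the Crohn's stratum. The article gives no rate of failed implantation and no prognosis for unsuitable tracts, so neither the frequency nor the direction of bias can be stated. If one unsuitable Crohn's control stays in, the healing difference in the plan's scenario is 0.167 larger than under symmetric handling when that control does not heal, and 0.167 smaller when that control heals. This rests on the assumed uniform priors for the bounds, one such control, and no refill. No claim is made about the single-arm primary proportion, and none of the article's stated figures is wrong on this account. It deserves an amendment because the remedy is cheap and a single participant matters among four controls.

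**What to change.** For participants still to be enrolled:

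1. Perform the same examination under anesthesia in both arms.
2. Record surgical eligibility before the assignment is drawn or revealed, within the existing baseline visit. Anyone unsuitable then leaves before randomization, whichever arm would have followed.
3. Analyse everyone by randomized arm and delete the sentence that restricts the intervention arm to those who receive the implant.

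Enrolment began in November 2024, so the order cannot be changed for those already randomized. For them, report by arm, with the reason, anyone randomized but not treated. Screen Failures already calls for recording the details; the breakdown by arm is the addition.

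The cost is amended wording and a reordering within one visit. The downside is that assignment takes place in the operating room, with both sets of materials on hand.

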### Administration

The following procedures will be performed by the surgeon for administration of the intervention.

A clinical examination under anesthesia with an anal fistula probe will be conducted to rule out active infection, anal stenosis, or active proctitis and confirm the presence of a single fistula tract.The seton will be removed, the fistula tract curetted vigorously to remove granulation tissue lining the tract, and the tract will be flushed with saline.The fistula tract length and diameter and amount of the sphincter muscle involved will be assessed by the surgeon with an anal fistula probe placed from the external to the internal opening.The appropriate model collagen matrix will be used based on the length of the tract.The collagen will be saturated with the rhPDGF solution in a sterile dish for a minimum of 10 min.After the collagen is fully saturated with rhPDGF, it will be pulled through the fistula tract carefully from the internal opening to the external opening.The collagen will be sutured to the rectal mucosa at the internal opening and any portion beyond the skin level will be trimmed to sit flush with the external opening.

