Supplementary analysis of this secondary endpoint will consider time in weeks to achieve complete healing from baseline up to 12 weeks. This endpoint will be determined by the self-reported measure of no leakage from the weekly participant survey and will be focused on the first achievement of complete healing, as recurrence will be assessed in other outcomes. This endpoint will be analyzed using a Cox proportional hazards model, conditional on the treatment arm and Crohn’s status as outlined in the SAP. The results will be presented as an adjusted hazard ratio and a marginal hazard ratio after performing standardization. Proportional hazards will not be checked with a hypothesis test, as this is typically not a recommended procedure; instead, Kaplan-Meier curves will be calculated, and plausibility of proportional hazards will be assessed visually. If proportional hazards are violated or model fit is poor, the outcome will be compared across arms using the log-rank test. Missing data are expected to be limited, but will be handled using multiple imputation, taking the longitudinal nature of surveys into account.

The next secondary endpoint is fistula recurrence at 6 months. This will be measured as the percentage of the total number of treated participants in each arm that were diagnosed as healed at Month 3 with subsequent recurrence of the fistula by clinical evaluation of the external opening at the Month 6 follow-up visit. This is a binary endpoint which will be analyzed using the same procedures as those outlined for the binary Month 3 healing endpoint.

The final secondary endpoint is the change in the severity of symptoms at Month 3 (adjusted for baseline), which will be calculated using the ordinal scale for each question in the weekly participant survey. Scores will be compared between arms using Mann-Whitney tests. A composite variable will be calculated as defined in the SAP and analyzed using ordinal logistic regression conditional on treatment arm, baseline score, and baseline etiology. The proportional odds assumption will be assessed using a parallel line plot. A longitudinal ordinal mixed effects model with similar specification and a random intercept for study participant and a linear time term will be used to compare longitudinal symptom severity over time. Results will be presented as adjusted odds ratios and missing data will be handled using multiple imputation.

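### Time to healing counts the first self-reported dry week as complete healing, and the recurrence endpoint cited to justify this does not cover relapse before Month 3

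*Protocol article*

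**What the plan says.** All of this stands in the Protocol article, under Secondary and Tertiary Outcomes Analysis unless another section is named.

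- **Status and window.** The analysis supplements the binary Month 3 healing endpoint and looks at "time in weeks to achieve complete healing from baseline up to 12 weeks".
- **Source of the event.** "This endpoint will be determined by the self-reported measure of no leakage from the weekly participant survey".
- **Which report counts.** The analysis "will be focused on the first achievement of complete healing, as recurrence will be assessed in other outcomes".
- **Model and fallback.** "This endpoint will be analyzed using a Cox proportional hazards model, conditional on the treatment arm and Crohn’s status as outlined in the SAP". Then: "If proportional hazards are violated or model fit is poor, the outcome will be compared across arms using the log-rank test".
- **Recurrence.** The one recurrence endpoint counts participants diagnosed as healed at Month 3 whose fistula is found to have recurred at the Month 6 examination. The Secondary outcomes section defines it in the same way.
- **Month 3 healing.** This is a clinical finding of no visible drainage. Under Randomization and Blinding, the examination is done by a surgeon who took no part in the screening visit or the procedure.
- **Adjustment.** The Statistical analysis section says that statistical models will be adjusted for Crohn's status.

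**The concern.** The word recurrence is asked to cover something that its definition excludes. The plan accepts the first dry report as healing because later failure is picked up elsewhere, but the recurrence endpoint opens only at Month 3. The time-to-healing window closes at 12 weeks, about the same point. A relapse inside that window falls between the two.

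A participant who reports no leakage in week 5, leaks again from week 6 and is draining at Month 3 would be completely healed at week 5 in the Cox model and not healed in the logistic model. If that participant is a control, the Crossovers section would also make them eligible for crossover because the fistula has not healed. Two analyses of one endpoint would then disagree through definition alone.

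The Sample Size section expects time to healing to have slightly higher power provided that the patient-reported data are accurate. A rule that turns on a single report is the version most exposed if that condition fails. With 8 and 4 participants, one or two false events matter.

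**Working it through.** The article gives no figure for time to healing, so there is none to reproduce. Its sample-size bounds (0.63, about −0.14, −0.01) do reproduce, at 0.631, −0.145 and −0.008, but they do not bear on this analysis.

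**Inputs**
- From the article: a 12-week window with weekly surveys, so 12 reports; 12 participants, 8 against 4; 50% healed at 3 months in the routine care arm; 9 Crohn's and 3 idiopathic participants expected, in blocks of 3 at 2:1.
- Assumed: *q*, the chance per week that a fistula that has not healed is reported as dry. The documents give no value, so a range from 2% to 20% is shown.

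**Step 1. Never-healed participant, weeks independent**

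P(at least one dry report in 12) = 1 − (1 − *q*)^12. For *q* = 0.05 this is 1 − 0.95^12 = 0.460.

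| *q* | First dry week | Two consecutive dry weeks | Dry through week 12 |
|---|---|---|---|
| 0.02 | 0.215 | 0.004 | 0.02 |
| 0.05 | 0.460 | 0.026 | 0.05 |
| 0.10 | 0.718 | 0.097 | 0.10 |
| 0.20 | 0.931 | 0.322 | 0.20 |

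The last column equals *q*, because a never-healed participant meets that rule only if the week 12 report happens to be dry. Censoring those still draining at the Month 3 examination removes these events too.

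**Step 2. Weeks correlated**

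Reports on one fistula are unlikely to be independent. Suppose that a dry week follows a dry week with probability 0.5, with the same marginal rate *q*. The chance of a dry week after a wet one is then *a* = 0.5*q*/(1 − *q*), and P(at least one dry) = 1 − (1 − *q*)(1 − *a*)^11.

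| *q* | *a* | First dry week | Two consecutive dry weeks |
|---|---|---|---|
| 0.05 | 0.0263 | 0.292 | 0.144 |
| 0.10 | 0.0556 | 0.520 | 0.277 |
| 0.20 | 0.125 | 0.816 | 0.507 |

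Correlation makes the problem smaller. It also weakens a two-week rule considerably. The sustained-to-week-12 rule still gives *q*.

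**Step 3. Effect on the comparison**

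Let 50% truly heal in each arm, at times uniform over weeks 4 to 12, with independent false-dry reports otherwise. The first-dry-week event proportion is 0.50 + 0.50 × 0.460 = 0.73 at *q* = 0.05, and 0.50 + 0.50 × 0.718 = 0.86 at *q* = 0.10. Large-sample Cox hazard ratios, intervention to control, from simulation:

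| *q*, intervention / control | First dry week | Dry through week 12 |
|---|---|---|
| 0.10 / 0.10 | 1.00 | 1.00 |
| 0.10 / 0.05 | 1.53 | 1.05 |
| 0.20 / 0.05 | 2.70 | 1.17 |
| 0.05 / 0.10 | 0.65 | 0.95 |

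The hazard ratio is biased only if *q* differs between arms, and the sign follows that difference. The sustained rule brings each biased ratio close to 1.

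**Step 4. Where the arms differ**

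The expected split gives 6 intervention and 3 control participants with Crohn's disease, and 2 and 1 with idiopathic fistulas. Crohn's controls have the seton removed and receive no implant, whereas the idiopathic control receives a commercial plug. The contrast between a filled and an unfilled tract therefore exists only in the Crohn's stratum, where 3 of the 4 expected controls fall.

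**Step 5. The fallback**

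The log-rank test is the score test of a Cox model containing arm alone. It is most powerful under proportional hazards and yields no effect estimate. Unstratified, it drops the Crohn's term.

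**The case against.** **The rule may be completed in the SAP.** The article does not say in so many words that one isolated report suffices, and a confirmation rule is often left to the SAP, which is not shown. That is fair as far as it goes. But the article itself fixes first achievement and gives a reason for it, and the reason does not hold. It refers to the SAP in the sentence on the Cox model, not for the event.

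**Early relapse is not lost.** A reader might infer that a relapse before Month 3 is recorded nowhere. The documents do not support that. Drainage at Month 3 makes the participant not healed in the main healing analysis, and renewed leakage enters the symptom scores and the longitudinal symptom model. None of these corrects the event in the Cox model, and none counts it as a recurrence.

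**The arm effect is not documented.** A reader might also infer that false events favour the intervention because its tract is filled. The Administration section says that "any portion beyond the skin level will be trimmed to sit flush with the external opening", but nothing in the article says what an implant does to early leakage. Idiopathic controls have a plug as well, and the Risks section allows for acute inflammation at the site, which could act the other way. The Discussion already concedes that the lack of a true placebo complicates the secondary outcomes. This objection stands in full.

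**The sizes depend on assumptions.** The weekly rates are assumed, and independence overstates both the problem and the gain from a two-week rule (Step 2). This also stands.

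**The log-rank test remains valid.** It tests equality of the curves without proportional hazards and can be computed if the Cox model fails to fit in 12 participants. That is true, and replacing it with an adjusted restricted mean in 8 against 4 would be debatable. The lost Crohn's adjustment remains.

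**Conclusion.** The point holds as a defect of definition. The event is the first dry self-report, no persistence or confirmation is stated, and the reason given does not cover relapse before Month 3. The result can contradict the clinical endpoint that it supplements.

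At assumed weekly false-dry rates of 5% to 10%, 46% to 72% of never-healed participants would be counted as healed if weeks are independent, and 29% to 52% under the correlation tried here. Bias between arms is possible in the Crohn's stratum, but neither its presence nor its direction is shown: equal rates give a hazard ratio of 1.00, and reversing 10% against 5% moves it from 1.53 to 0.65.

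The consequence is limited to a supplementary analysis in a 12-participant pilot. The primary endpoint and the Month 3 healing endpoint are not affected.

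**What to change.** 1. Define the event as the first week of no leakage that is sustained through the last weekly survey up to Month 3. Censor everyone else at week 12, including participants still draining at the Month 3 examination.
2. Keep the first-dry-week version as a labelled sensitivity analysis.
3. Drop or reword the statement that recurrence is assessed in other outcomes, since the recurrence endpoint begins at Month 3.
4. If the log-rank fallback is used, stratify it by Crohn's status, and say that it tests equality of the curves and does not itself remedy non-proportional hazards.

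This is a change of wording and needs no new data. The cost is fewer events and less information independent of the Month 3 binary endpoint, because each event now requires no drainage at that examination. One mistaken or spotty late report can also move or cancel an event. The sensitivity analysis retains the finer-grained view for readers who want it.
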